We take the knee abduction moment and the loading rate of knee abduction moment over time as the main variables of interest as the main training purpose of this study is to get alignment of the leg in line with the GRF. When taking the clinical relevance of an 'at risk' and a 'not at risk' abduction moment into account, we refer to the prospective study by Hewett et al. [61]. The females in that study who ruptured their ACL (n = 9) had a greater stance phase peak external knee abduction moment, -45.3 ± 28.5 Nm, compared to that of uninjured females (n = 390), -18.4 ± 15.6 Nm (P < 0.001). We considered this mean difference in knee abduction moment to be clinically relevant, as it was predictive of ACL injury occurrence in a prospective study. We therefore used the difference to calculate the power for this study. With an effect size of 0.55 (determined based on those differences of the means divided by the pooled SD) and an alpha of 0.05, we reach a power of 0.80 when including 120 subjects, which means 40 subjects (20 females and 20 males) per group (ie. implicit learning group, explicit learning group and control group). G*Power for Mac, Version 3.1.2 has been used to calculate the needed sample size.

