### Intervention

Two types of immediate visual feedback will be given (Table 1):

**Table 1 T1:** Testing schedule

	Explicit Learning Group (n = 40)	Implicit Learning Group (n = 40)	Control Group (n = 40)
T1 Intervention	30 side-step cutting trials - Detailed verbal instructions on performance will be given	30 side-step cutting trials - Best performance will be shown	30 side-step cutting trials - No feedback on performance will be given
T2 Retention test (one week post intervention)	30 side-step cutting trials - No feedback on performance will be given	30 side-step cutting trials - No feedback on performance will be given	30 side-step cutting trials - No feedback on performance will be given
T3 Retention test (one month post intervention)	30 side-step cutting trials - No feedback on performance will be given	30 side-step cutting trials - No feedback on performance will be given	30 side-step cutting trials - No feedback on performance will be given

1) Explicit feedback: After each sidestep cutting manoeuvre, subjects will immediately receive explicit instructions to improve their performance. Potential ACL injury risk factors include: 1) Increased knee valgus angle [61], 2) Decreased knee flexion angle [62-64], 3) Increased anterior tibial shear force [65,66], 4) Decreased hip flexion angle [62,64,67,68], 5) Increased hip internal rotation angle [62], 6) Increased knee internal rotation angle [69]. Items to improve these potential risk factors above will be mentioned to the subjects and subjects will be requested to minimise the load at the knee.

2) Implicit feedback: Subjects will undergo a dynamic visual feedback intervention. Each time after a subject has performed the task, a visual representation of the best performance so far of the whole body (3D posterior view) will be shown to the subject with the Basler recordings (Darwinian learning). No explicit feedback or instructions at all will be given, however subjects will know in advance that there are superior and inferior ways to perform the task. The subject will search by him-/herself for the solution that fits best in their body; they explore and then select the performance which fits best.

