### Measurements

Screening for inclusion and exclusion criteria will occur at the laboratory setting and will be performed by the primary investigator ([name]) of this study. All subjects will sign an informed consent form in accordance with the University of Groningen Medical Ethics Committee prior to participation.

Lower extremity kinematic, kinetic and EMG data of subjects performing a sidestep-cutting manoeuvre in the laboratory will be analysed. The primary outcome measurements will be as follows:

1) Knee abduction moment

2) Loading rate of knee abduction moment over time

Secondary outcome parameters will be as follows:

3) Average EMG pattern of the gluteus maximus (GM), vastus medialis (VM), vastus

lateralis (VL), medial hamstring (MH), lateral hamstring (LH), medial gastrocnemius

(MG) and lateral gastrocnemius (LG)

4) Muscle onset time (ie. the first burst in EMG as detected by the Santello algoritm prior

to landing [66]) of the GM, VM, VL, MH, LH, MG and LG

5) Muscle activity of the GM, VM, VL, MH, LH, MG and LG integrated over the interval from 100 milliseconds prior to foot contact to foot contact (preparatory interval) and from foot contact to the point of peak knee flexion (weight acceptance)

6) Muscle co-contraction (ie. using the integrated EMG of each muscle and the formula: [(less active muscle/more active muscle) X (sum of the integrated activity of both muscles)]) of VL-MG, VL-LH, VM-LG and VM-MH over the interval from 100 milliseconds prior to foot contact to foot contact (preparatory interval) and from foot contact to the point of peak knee flexion (weight acceptance)

7) Hip, knee and ankle angles at IC, peak posterior GRF and the maximum values for each of those variables

a. Abduction/adduction

b. Flexion/extension

c. External/internal rotation (only for hip and knee)

8) Knee angular displacement flexion angle

9) Joint moments of hip, knee and ankle at IC, peak posterior GRF and the maximum values for each of those variables

a. Abduction/adduction (not for knee, see primary outcome measurement)

b. Flexion/extension

c. External/internal rotation (only for hip and knee)

In addition we will record the history on injuries and/or surgeries, the Tegner activity level questionnaire [69,70] and activity between intervention and follow up tests.

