### Data acquisition and statistical analysis

Hip, knee and ankle joint kinematics will be evaluated at IC, peak posterior GRF and the maximum values for each of those variables. IC will be defined as the point in time when 5% of the subject's body weight is upon the force plate. The raw coordinate data will be filtered using an optimised cut off frequency.

Raw analog data from the MVICs and synchronised raw analog data (joint kinematic, joint kinetic data and GRF data) from the jump trials will be imported into Matlab (release 12, The MathWorks, Natick, MA) for data processing and identification of the variables of interest. The mean value of each MVIC will be used for normalisation of the EMG during the jump trials. Both the MVIC and trial EMG data will be processed with a linear envelope before filtering by a Butterworth filter (fourth-order, zero-phase shift, cut off frequency of 20 Hz).

Raw analog data from the force plates will be used to calculate the GRF data for each jump trial. The raw coordinate data will be filtered using an optimised cut off frequency. The GRF will be filtered using a fourth-order Butterworth filter at a cut off frequency of 100 Hz. The GRF data will be used to calculate the maximum posterior GRF during the initial-stance phase of the jump tasks.

Only the dominant leg will be analysed. In addition to the 30 trials during the intervention and retention tests, all subjects will perform five trials to begin with. These five baseline trials (without feedback) prior to the intervention will be conducted to assure homogeneity across groups on the primary outcome measures (knee abduction moment and the loading rate of knee abduction moment over time). The results of these five trials will be compared to each other using a one-way ANOVA. Multilevel analysis will be applied to examine the within and between subject effects. The learning curve with implicit versus explicit versus no feedback of the primary outcome measures over time will be analysed using SPSS 18.0 (SPSS Inc., Chicago, IL). The secondary outcome measurements will be used as explanatory variables. In addition, post-hoc Bonferroni adjustments will be conducted for the within, between and interaction effects. An alpha level of 0.05 will be set a priori.

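### Secondary outcomes recorded during or after feedback are named as explanatory variables beside the only described group analysis, without saying that the group test excludes them

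*Protocol article*

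**What the plan says.** The section on data acquisition and statistical analysis gives the method for the primary outcomes in three consecutive sentences:

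- The first calls for a multilevel model that separates effects within subjects from those between them.
- The second names what is compared: "The learning curve with implicit versus explicit versus no feedback of the primary outcome measures over time will be analysed using SPSS 18.0"
- The third gives the secondary outcomes their role: "The secondary outcome measurements will be used as explanatory variables"

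The Study population section names the primary outcomes: "We take the knee abduction moment and the loading rate of knee abduction moment over time as the main variables of interest".

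The Measurements section lists the secondary outcomes. They are EMG measures (average pattern, onset, integrated activity, co-contraction), knee flexion displacement, "Hip, knee and ankle angles at IC, peak posterior GRF and the maximum values for each of those variables", and, as a further item on its list, "Joint moments of hip, knee and ankle at IC, peak posterior GRF and the maximum values for each of those variables". All come from the same cutting manoeuvre as the primary outcomes.

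The Intervention section lists six risk factors for the explicit arm and says: "Items to improve these potential risk factors above will be mentioned to the subjects". The implicit arm gets no instruction but is shown its best trial so far, chosen by lowest peak valgus moment.

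**The concern.** The trial asks whether feedback lowers the knee abduction moment and its loading rate, by whatever route. Feedback can only do this by changing how the athlete moves, and the secondary outcomes measure how the athlete moves. If they stand beside feedback group in the same model, the group coefficient no longer answers that question. It becomes the difference between arms at equal joint angles, joint moments and muscle activity, which is the part of the effect that bypasses movement pattern. A method that works as intended could then show a small group effect.

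There is a second risk. These variables are affected by the randomised feedback. If an unmeasured trait drives both a secondary outcome and the abduction moment, conditioning on that outcome can create a group difference where none exists.

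**Working it through.** **Are the variables on the causal path?** Of the six risk factors in the explicit-feedback list, five are joint angles that return as secondary outcome 7:

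| Explicit-feedback target | Secondary outcome |
|---|---|
| Knee valgus | 7a, knee abduction/adduction |
| Knee flexion | 7b, knee |
| Hip flexion | 7b, hip |
| Hip internal rotation | 7c, hip |
| Knee internal rotation | 7c, knee |

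The sixth, anterior tibial shear force, is not on the secondary list. The implicit arm would also work through changed movement, since it is shown the trial with the lowest valgus moment.

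**Could baseline values be meant?** The article uses the five pre-feedback trials only to check that the groups are alike on the primary outcomes. Nothing limits the explanatory variables to those trials.

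**The plan's own figure.** The Study population section gives effect size 0.55, alpha 0.05, power 0.80 and 120 subjects (40 per group). A one-sided comparison of two arms comes close: 41 per arm by the normal formula, and power 0.79 at 40 per arm. A two-sided t-test at 40 v 40 gives 0.68, which is the reference value below.

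**Effect of adjusting.** Inputs from the article: 40 per arm and effect size 0.55. The SD follows from its quoted figures: √[(8 × 28.5² + 389 × 15.6²)/397] = 15.96, rounded to 16 Nm, so 0.55 × 16 = 8.8 Nm. Assumptions: one mediator M, one value per subject, two-sided 0.05, and M explaining half of the within-arm variance (ρ² = 0.5).

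In SD units let M = aG + noise and Y = ρM + cG + error, with G the arm. The total effect is c + aρ = 0.55 and the mediated share is m = aρ/0.55. Then:

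- Without M: estimate 0.55; standard error √(2/40) = 0.224; ratio 2.46; power 0.68.
- With M: estimate c = 0.55(1 − m); standard error √[(2/40) × 0.5 × (1 + a²/4)], with a = 0.55m/0.707.

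| Share mediated | a | Estimate, SD | Estimate, Nm | Standard error, SD | Ratio | Power |
|---|---|---|---|---|---|---|
| 0% | 0 | 0.55 | 8.8 | 0.158 | 3.48 | 0.93 |
| 25% | 0.19 | 0.41 | 6.6 | 0.159 | 2.60 | 0.73 |
| 50% | 0.39 | 0.275 | 4.4 | 0.161 | 1.71 | 0.39 |
| 70% | 0.54 | 0.165 | 2.6 | 0.164 | 1.01 | 0.17 |
| 100% | 0.78 | 0 | 0 | 0.170 | 0 | 0.05 |

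With a weaker mediator (within-arm correlation 0.5, simulated), power is 0.80 at 0%, 0.54 at 25%, 0.26 at 50%, 0.10 at 75% and about 0.05 at 100%.

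**Bias when feedback has no effect.** Let an unmeasured cause load 0.7 on both M and Y (an assumption), and let feedback shift M but not Y. The adjusted group coefficient is −a × 0.7². A shift of 0.55 SD gives −0.27 SD, and a shift of 1.0 SD gives −0.49 SD. Simulated false-positive rates are 0.25 and 0.60.

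**The case against.** The best defence is that the sentence does not say which model it means. The Study design section defines the design by gender, intervention group and time, with no covariates, and the Bonferroni adjustment is attached to effects of that structure. The primary test could therefore contain only those factors, with the secondary outcomes used afterwards to explain how the moment changed. That would be a legitimate analysis, and a condensed article may leave exact model terms to a fuller plan. This stands as a possible reading. It does not remove the point, because the article does not merely omit a detail. It gives the secondary outcomes a role immediately after the only described group analysis and does not separate the two.

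The numbers also need their limits. At low mediated shares adjustment raises power, because M removes residual variance: 0.93 at 0% and 0.73 at 25%, against 0.68 unadjusted. At 25% the estimate is still a quarter too small. The 8.8 Nm is also not the difference the article calls clinically relevant, which is 45.3 − 18.4 = 26.9 Nm. With that effect in the same setting, adjusted power is about 0.99 at 50% mediated and about two thirds at 70%. The proportional shrinkage of the estimate is unchanged.

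A reader might go further and count the secondary variables: 7 EMG patterns, 7 onsets, 14 activities, 8 co-contractions, 24 angles, 1 displacement and 21 moments, 82 in all, against 120 subjects. The article does not support a charge of overfitting on that ratio. It does not say that all 82 enter one model, and the multilevel analysis can draw on 30 trials in each of three sessions.

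**Conclusion.** The point holds as a badly fixed rule. Followed on its plain reading, it conditions the comparison of feedback groups on variables through which feedback is meant to act.

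A reader might infer that the trial therefore cannot answer its main question. The article does not support that. It does not state outright that the secondary outcomes enter the model testing the group effect, and complete loss of the effect requires complete mediation.

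Under the plain reading, the estimate shrinks in proportion to the mediated share, from no loss at 0% to total loss at 100%. It can also be biased when there is no effect at all. The mediated share, the strength of the mediator and the common-cause loadings are assumptions, and the single-mediator calculation simplifies the multilevel model. The direction of the shrinkage rests on less: only on the secondary outcomes carrying part of the effect, which the overlap between the explicit-feedback targets and secondary outcome 7 makes likely.

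**What to change.** Replace the sentence with two:

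1. The group and group-by-time effects on both primary outcomes are tested in a multilevel model with no variable measured after feedback starts; gender and the baseline value of the outcome may be included.
2. Any model relating the secondary outcomes to the knee abduction moment is a separate, exploratory mechanism analysis.

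If a separate analysis was always intended, this simply says so. It needs no extra data, changes no sample size and drops no planned analysis.

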## Methods/Design

### Study design

This will be a randomised controlled laboratory study with two between-subject factors (gender and intervention group (ie. implicit, explicit and control group)) and one within-subject factor (time, ie. pretest, one week posttest and one month posttest). After consent to participate, subjects will be randomly assigned to a group based on the order in which they sign up for the initial baseline testing session. As an equal number of males and females per group (2 × intervention group and 1 × control group) is essential, stratified sampling will be carried out. The study design, procedures and informed consent are approved by the local Medical Ethical Committee (registration number 2009-142).

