The best performance so far will be based on the peak valgus moment, which needs to be as low as possible. The total training session consists of 30 trials. As we need to make sure that the improvements in landing performance (if any) are permanent rather than temporary, a retention test will be conducted one week (similar to Onate et al.) [70] and one month later. During the retention tests no feedback at all will be given to either group. The control group will perform the exact same tasks as the intervention groups. The control group, however, will not receive any feedback during any trial. To make sure three homogeneous groups are participating, five trials with no feedback will be performed prior to the real intervention (ie. in addition to the 30 trials).

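### Two equal primary outcomes share one undivided alpha of 0.05, and the stated Bonferroni rule does not reach across them: if either can carry the conclusion, the familywise error is above 0.05 and at most 0.0975

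*Protocol article*

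**What the plan says.** All references are to the protocol article.

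- **Two primary outcomes.** Study population, in the sample-size paragraph: "We take the knee abduction moment and the loading rate of knee abduction moment over time as the main variables of interest". Measurements lists the same two as primary, and Data acquisition and statistical analysis again calls both of them primary. None of these places ranks one above the other.
- **One alpha.** Data acquisition and statistical analysis: "An alpha level of 0.05 will be set a priori".
- **One multiplicity rule.** Same section: "post-hoc Bonferroni adjustments will be conducted for the within, between and interaction effects".
- **The factors those effects come from.** Study design names gender and intervention group as between-subject factors, and "one within-subject factor (time, ie. pretest, one week posttest and one month posttest" as the within-subject factor. The analysis is described thus: "Multilevel analysis will be applied to examine the within and between subject effects".
- **Definition of the first outcome.** Measurements gives it by name only, without an instant. Secondary item 9 covers "Joint moments of hip, knee and ankle at IC, peak posterior GRF and the maximum values for each of those variables" but removes the knee from its first sub-item: "Abduction/adduction (not for knee, see primary outcome measurement". Two other places do use a peak. The sample size rests on a difference in stance-phase peak external knee abduction moment, and Intervention says "The best performance so far will be based on the peak valgus moment".
- **Sample size.** Effect size 0.55, alpha 0.05, power 0.80 and 120 subjects (40 per group), argued from the abduction moment alone.

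**The concern.** The article does address multiplicity, but the scope it gives the adjustment omits the two primary outcomes. Outcome is not a factor in the model, so Bonferroni over the within, between and interaction effects is applied separately for each outcome, and each outcome then has its own 0.05. With no order or success rule, an analyst who follows the text can report a positive trial on whichever outcome reaches significance. The Discussion says the results will be applied to future injury prevention programs, so it matters which error rate stands behind a positive claim.

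A smaller gap adds to this. The cross-reference in item 9 sends the reader to a primary outcome that has no instant attached, so the quantity that should lead the analysis has to be inferred from the sample-size and feedback text.

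**Working it through.** **Inputs.** Alpha 0.05 (Data acquisition and statistical analysis); two primary outcomes (Study population; Measurements); effect size d = 0.55, 40 per group and power 0.80 (Study population). The article gives no correlation between the two test statistics, so I assume a range. I take d = 0.55 as stated.

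**Step 1: the plan's own power figure.** The article does not state the test or its sidedness. At d = 0.55 and alpha 0.05:
- two-sided t test, 40 v 40: power 0.68
- one-sided t test, 40 v 40: power 0.79
- two-sided t test, 40 v 80 (control against both feedback groups pooled): power 0.80

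The stated 0.80 is thus reached with pooled feedback groups, or nearly so one-sided. Each of these uses the full 0.05 on one outcome, so the sample size makes no allowance for a second primary outcome.

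**Step 2: familywise error over the two outcomes.** If each outcome is held at two-sided 0.05 and either suffices, then

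FWER = 1 − P(|Z1| ≤ 1.96 and |Z2| ≤ 1.96).

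Independent tests: 1 − 0.95² = 1 − 0.9025 = 0.0975. For correlated, jointly normal statistics, by numerical integration:

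| Assumed correlation | FWER |
|---|---|
| 0 | 0.0975 |
| 0.3 | 0.095 |
| 0.5 | 0.091 |
| 0.7 | 0.083 |
| 0.9 | 0.070 |

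The loading rate is derived from the same moment curve, so positive correlation is likely and the lower rows are more plausible than the first.

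**Step 3: does the promised Bonferroni close the gap?** Credit it fully over two retention contrasts, so that each is tested at 0.05/2 = 0.025 within each outcome. With all four tests independent, FWER = 1 − 0.975⁴ = 1 − 0.9037 = 0.096. Simulation with correlation between outcomes up to 0.9 and between visits up to 0.7 brings this down to 0.061 at the lowest. The rule does its job within an outcome, and the excess across the two outcomes remains.

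**Step 4: what each remedy does.**
- *Fixed sequence, moment first.* If the moment has no true effect, any false claim requires a false rejection on the moment, with probability at most 0.05. If the moment has a true effect, only the loading rate can be falsely rejected, again with probability at most 0.05. FWER is therefore at most 0.05, and the moment keeps its full alpha.
- *Split or Holm.* At 0.025 each, FWER is at most 2 × 0.025 = 0.05. Two-sided power for a two-group contrast at d = 0.55 and 40 per group falls from 0.68 to 0.57. By the normal approximation, n = 2(z₁₋α/₂ + z₀.₈)²/d², so 80% power needs 2(1.960 + 0.842)²/0.3025 = 52 per group at 0.05 and 2(2.241 + 0.842)²/0.3025 = 63 at 0.025.

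**The case against.** The strongest objection concerns scope. This is a journal article, and an order or alpha split for two primary outcomes may stand in a fuller protocol or analysis plan that is not shown. The article also states no success criterion, and a rule requiring both outcomes to succeed would not inflate the error at all. This part stands as a condition: the inflation arises only if either outcome suffices. It does not remove the point, because the article is not silent on multiplicity. It states an adjustment and its scope, and that scope leaves out the two outcomes.

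A reader might also infer stronger versions that the article does not support:

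- **That the one-week and one-month tests are uncontrolled.** Time is the within-subject factor, so contrasts between visits and group-by-time effects fall under the promised Bonferroni. No separate 0.05 test at each visit is described.
- **That the abduction moment will be tested at three instants.** Four independent tests (three instants plus loading rate) would give 1 − 0.95⁴ = 0.185, but this matches no planned analysis. Item 9 takes the knee abduction moment out of the three-instant list, and the sample-size and feedback text both use the peak. What remains is a definition that should state the peak.
- **That one month is the decisive visit.** Intervention uses both retention tests to judge whether improvement lasts and does not favour one.
- **That the trial misstates its false-positive rate by a factor of two.** The article states an alpha level, not a trial-wide error rate, and 0.0975 is the value for independent tests.

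**Conclusion.** The point holds in a limited form. Two primary outcomes of equal rank are tested at one undivided alpha, and the stated Bonferroni rule works within each outcome's model but not across the two. If either outcome can carry the conclusion, the familywise error is above 0.05 and at most 0.0975, and about 0.07 to 0.09 at correlations of 0.9 to 0.5. This rests on three assumptions: an either-outcome success rule, which the article neither states nor excludes; jointly normal two-sided tests; and correlations that the article does not give. The excess is moderate and should be corrected, since the correction is cheap. The missing instant in the definition of the first outcome is a matter of wording and belongs in the same edit.

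**What to change.** In Measurements, define the first primary outcome as the peak stance-phase external knee abduction moment. In Data acquisition and statistical analysis, state that it is tested first at 0.05, and that the loading rate is tested confirmatorily at 0.05 only if the moment is significant; otherwise the loading rate is reported descriptively. Say which model effect opens the second test. The natural candidate is the group-by-time interaction, since the article describes the analysis as comparing learning curves over time across the three groups. Keep the existing Bonferroni rule for the group and retention-time contrasts within each outcome.

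**Cost.** The moment loses no power and the sample size does not change. The loading rate loses its stand-alone primary status: a clear effect on it alone could no longer be claimed as confirmatory.

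**Alternative.** If the investigators want either outcome to be able to succeed alone, use Holm across the two. The moment is then tested at 0.025 unless the loading rate has already been rejected at that level, so two-group power at d = 0.55 and 40 per group could fall from 0.68 to as low as 0.57.
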